## Synopsis

### COLD PLASMA THERAPY FOR ACCELERATION OF WOUND HEALING IN DIABETIC FOOT

|                                    |                                                                                                                                                                                                                                                                                                                                                                                                                                                                                                                                                                                                                                                                                                                                                                                                                                         |
|------------------------------------|-----------------------------------------------------------------------------------------------------------------------------------------------------------------------------------------------------------------------------------------------------------------------------------------------------------------------------------------------------------------------------------------------------------------------------------------------------------------------------------------------------------------------------------------------------------------------------------------------------------------------------------------------------------------------------------------------------------------------------------------------------------------------------------------------------------------------------------------|
| V1.3 as of 05/JUL/2016             | STUDY-NO.: KPW2016-1.1                                                                                                                                                                                                                                                                                                                                                                                                                                                                                                                                                                                                                                                                                                                                                                                                                  |
| Objective                          | People with diabetes mellitus present with a higher risk of developing chronic wounds. A reduced pain sensation resulting from neuropathy often accounts for wounding. Therefore, people with diabetes show higher risks for late complications like limb amputation, which causes loss of life quality and increased mortality. Main objective of this study is to determine, whether application of cold plasma could significantly improve wound healing.                                                                                                                                                                                                                                                                                                                                                                            |
| Study design                       | This study will be conducted as a bi-center, randomized, patient-blinded study with a certified medical device. For determination whether cold plasma application in patients with diabetes and diabetic foot Wagner-Armstrong stage 1B or 2B as well as ulcer curis may accelerate wound healing, people presenting with either type 1 or type 2 diabetes mellitus will be randomized to plasma or placebo therapy, respectively. Each group should be comparable according to age, gender and ulcer-stadium.                                                                                                                                                                                                                                                                                                                          |
| No. of patients/ duration of study | A dropout rate of 10% is assumed for this study. 66 patient wounds will be recruited to result in 60 evaluable data sets. Study procedures will be performed at HDZ NRW in Bad Oeynhausen and at Klinikum Karlsburg in Karlsburg. Patient wounds will be equally assigned to both treatment groups (plasma and placebo) via stratified randomization. Patient being hospitalized for treatment of diabetic foot (Wagner-Armstrong stage 1B or 2B) are in focus of the study which is carried out in a hospital setting. The study is planned to take approximately 8 months comprising 8 applications (5 on consecutive days, 3 afterwards in every second day manner). Follow up evaluations are planned after 1, 2 and 5 years after the first application to evaluate therapeutic side effects and long-term effects of the therapy. |
| Key inclusion criteria             | 
 
▪ Diabetes mellitus Typ 1/ Diabetes mellitus Typ 2
 
▪ HbA1c <math>\leq</math> 10%
 
▪ Age 18 – 80 years
 
▪ Ulcus Wagner-Armstrong 1B bzw. 2B (persistent for at least 3 weeks, no healing tendency)
 
                                                                                                                                                                                                                                                                                                                                                                                                                                                                                                                                                            |
| Key exclusion criteria             | 
 
▪ Participation in another clinical study with an IP during the last month prior to enrolment
 
▪ Wound treatment by local VAC-therapy, maggot therapy
 
▪ Essential dialysis therapy
 
▪ Application of topical antibiotics
 
▪ Treatment with platelet rich fibrin (PRF)
 
▪ Critical limb ischemia, defined as ankle brachial index below 0.5 or transcutaneous oxygen pressure below 15 mmHg.
 
                                                                                                                                                                                                                                                                                                                                                  |

## Time schedule

|                                      | Day 1 | Day 2-4 | Day 5 | Day 7 | Day 9 | Day 12 | Day 14 | Year 1 | Year 3 | Year 5 |
|--------------------------------------|-------|---------|-------|-------|-------|--------|--------|--------|--------|--------|
| Visit-No.                            | 1     | 2-4     | 5     | 6     | 7     | 8      | 9      | 10     | 11     | 12     |
| In-/Exclusion criteria               | x     | -       | -     | -     | -     | -      | -      | -      | -      | -      |
| Informed consent                     | x     | -       | -     | -     | -     | -      | -      | -      | -      | -      |
| Randomization                        | x     | -       | -     | -     | -     | -      | -      | -      | -      | -      |
| Wound documentation*                 | x     | x       | x     | x     | x     | x      | x      | x      | x      | x      |
| Mikrobiology (swap)                  | x     | -       | x     | x     | -     | x      | x      | -      | -      | -      |
| Local infection signs                | x     | x       | x     | x     | x     | x      | x      | -      | -      | -      |
| Sampling biomaterial wound dressings | x     | x       | x     | x     | x     | x      | x      | -      | -      | -      |
| Questionnaire SF-12                  | x     | -       | -     | -     | -     | -      | x      | x      | x      | x      |
| Questionnaire EQ5D                   | x     | -       | -     | -     | -     | -      | x      | x      | x      | x      |
| Visual analog scales                 | x     | -       | -     | x     | -     | -      | x      | x      | x      | x      |
| treatment                            | x     | x       | x     | x     | x     | x      | -      | -      | -      | -      |
| Documentation of side effects        | x     | x       | x     | x     | x     | x      | x      | x      | x      | x      |
| Standard wound care                  | x     | x       | x     | x     | x     | x      | x      | -      | -      | -      |

\* before therapy, surface measurement and photo documentation; at V10, V11, V12 documentation at original site were wound has been, if absent

## 1. Introduction

People with diabetes mellitus present with increased risk for superficial chronic wounds due to the presence of nerve impairments and reduced pain sensation (1, 2). 70-100% of patients with chronic wounds show symptoms of peripheral neuropathy. 0.8 to 10% of people with diabetes suffer from diabetic foot (DF), the yearly occurrence rate is 2,2–5,9% (3). Up to 30% of all diabetics show sensomotoric or autonomic neuropathy. All functional aspects of peripheral nerves are damaged by prolonged hyperglycemia. Because sensation for contact, pain and temperature is reduced or even lost, such stressors are not recognized, own protection mechanisms are lost. In addition, deep sensibility is reduced as well. Disequilibrium and imbalanced walking with abnormal biomechanical load induces pressure ulcerations (4, 5).

Co-existence of peripheral artery disease (PAD) and polyneuropathy causes less perfusion and nutrition in the wound area resulting in reduced healing. In most cases neuropathy and PAD, together, account for wound chronification. Superficial microbial load is common in diabetic foot, requiring antiseptic treatment and regular changes of dressings. Due to decreased pain sensation caused by neuropathy PAD is often diagnosed at advanced stages with concomitant occurrence of ulcerations or gangrene. Sometimes even simple wounds or short trauma develop to chronic wounds (6).

### 1.1 Therapeutic interventions

#### Off-loading

Beside improvements in the perfusion off-loading represents a key element in modern wound treatment. Bed-rest, use of crutches, or wheel chair are commonly applied. Orthopedic shoes up to total contact casts (TCC) are prescribed; orthoses are of comparable function if consequently worn by the patient (3).

#### Wound treatment

Debridement of avital necrotic wound tissue is essential in modern wound treatment to prepare optimal wound conditions. Debridement can be performed manually, enzymatically, or biologically using maggot therapy. The extent of procedures varies from case to case and may comprise local removal of affected fiber or bone. Local vacuum therapy can be applied to stimulate wound granulation and to remove exudation (7).

#### Wound disinfection

Each change of dressings should include antiseptic wound treatment (if infection is present) at least wound cleaning for biofilm removal. Moisture wound dressings are common for chronic wound treatment, a local temperature of at least 28°C is necessary for cell proliferation. Systemic antibiotic treatment has to be applied if clearly detectable proliferative bacterial load is present, whereas topic antibiotics are less effective (8).

#### Cold atmospheric plasma

Physical plasma is a highly reactive, ionized gas. Combination of several effective components of the plasma, such as reactive species derived from oxygen and nitrogen, a mild UV radiation, a mild current flow, and an increased temperature at the application site account for the antiseptic effect (8, 9). Through the interaction with molecules from air, body fluids, or target tissue active components are distributed in the target zone (7, 10). Currently, the exact mechanisms of action are poorly understood, but reactive oxygen species are thought to play a major role (11). Physical deteriorations caused by UV radiation or thermal stress are neglectable (7, 12).

Application of cold atmospheric plasma via plasma jet (kINPen® MED) is suitable for chronic, infected wounds like ulcer cruris or decubital ulcer, and pathogenic skin irritations (Acne vulgaris or Tinea pedis).

During application wound healing is supported by improved cell proliferation and antimicrobial effects. The plasma jet produces a handwarm plasma of good compatibility, that is painfree and easy to handle (7). During clinical routine use no negative side effects have been detected.

## 2. Objectives of the study

The objective of the study is to demonstrate an improvement in wound healing in diabetic foot by application of cold atmospheric plasma. Patient with either type 1 or type 2 diabetes mellitus will be randomized to receive plasma or placebo therapy. Each wound will be randomized separately. Eligible participants present with at least one chronic wound persisting for at least three weeks without healing tendency under standard wound care.

### Study flow scheme

[figure not shown]

R=Randomization  
EOS= End of Study

 Screening: Wound status, sample of materials

 EOS: questionnaires, Wound status, sample of materials

 time frame  $\pm 1$  day

 time frame  $\pm 30$  days

## **2.1 primary objectives**

- change in wound surface area
- change in signs of clinical infection
- change in microbial load

## **2.2 Secondary Outcome Measures**

- time to significant wound surface area change (time to 10% reduction of wound surface compared to treatment start)
- total wound surface change during treatment
- time to change in wound infection
- changes in Quality of life (EQ5D questionnaire)
- changes in Quality of life (SF12 questionnaire)
- Evaluation of symptoms during therapy (visual analog scale)
- treatment related side effects - formation of keloids, presence of skin irritation, local bleeding, proliferative skin reaction

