## **3 Study-design**

### **3.1 General design**

This study is a prospective, randomized, patient-blinded, placebo controlled bi-center study. The study will evaluate whether application of cold atmospheric plasma will accelerate wound healing in diabetic foot patients presenting with wound Wagner-Armstrong 1B or 2B.

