## **7 potential risk**

According to current knowledge application of cold atmospheric plasma is not associated with negative clinical side effects. Thus, no additional risk for the participants is to be awaited. Cold plasma therapy is used for the treatment of superficial skin diseases like acne, scars or cicatrices. Even from the therapy of tumors positive effects have been described. Cellular impairments caused by UV-radiation or thermal stress was excluded in clinical studies (7, 12). The application of cold plasma will be performed only by trained personal at both study sites. The device in use is CE-certified and licensed for the superficial skin treatment (kINPen® Med, Appendix 1).

Treatment is planned as an ad on treatment to standard wound care performed during the hospital stay of the patients. Thus, for both groups, plasma as well as placebo, no further risk is awaited. To current knowledge, patients feel no pain during treatment and potential therapy associated risks are of low occurrence.

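### The only safety outcome is worded as side effects related to treatment in a patient-blinded trial, so it can be read as counting only attributed events, and attribution may differ by arm

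*Protocol*

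**What the plan says.** Section 2.2 lists the safety outcome last among the secondary outcomes: "treatment related side effects - formation of keloids, presence of skin irritation, local bleeding, proliferative skin reaction". No other outcome covers safety, and none counts events regardless of cause. The protocol gives no criteria for relatedness and does not say who would judge it.

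Section 3.1 calls the trial a "prospective, randomized, patient-blinded, placebo controlled bi-center study". The synopsis agrees: "This study will be conducted as a bi-center, randomized, patient-blinded study with a certified medical device". Neither describes blinding of the operator, the investigator or an outcome assessor. Section 7 adds: "The application of cold plasma will be performed only by trained personal at both study sites".

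Section 7 also states an expectation: "According to current knowledge application of cold atmospheric plasma is not associated with negative clinical side effects". It goes on to say that plasma is given on top of standard wound care.

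The visit schedule has a row headed "Documentation of side effects", marked at all visits from 1 to 12. That row does not restrict the events to those related to treatment. The synopsis names side effects as one reason for the multi-year follow-up.

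**The concern.** A randomised comparison of side effects is fair when events are counted by the same rule in both arms. A relatedness condition adds a judgement between the event and the count. If the person judging knows the arm, the randomisation no longer protects the comparison, because the judgement itself can depend on the arm.

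Background events are likely in both arms. Bleeding and skin irritation can follow from dressing changes and debridement, and the placebo arm is there to measure that background. A relatedness condition could remove it.

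The bias could go either way. An assessor might attribute events more readily after plasma than after placebo, which would create an apparent excess. An assessor who shares the expectation in section 7 might discount events after plasma, which would hide a real excess. The protocol presents the treatment as essentially free of side effects, and this outcome is the trial's only defined randomised evidence on that point.

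**Working it through.** **Step 1: what the wording can mean.** Two readings fit section 2.2.

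- Reading A: an event counts only if it is judged to be caused by treatment.
- Reading B: the four named reactions are the effects of interest and are recorded as present or absent.

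The dash followed by a list leaves room for B. Section 8.2 supports A: it uses the same qualifier for adverse events that could stop the trial, and there the sense is causal. Nothing in the protocol settles the matter.

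**Step 2: inputs for reading A.** The protocol states no side-effect rate, so there is no figure of its own to reproduce. Its one usable input is 30 wounds per group to be analysed (section 3.2). The true event rate and the shares judged related are assumptions.

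**Step 3: formula.** In each arm:

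reported rate = true rate × share of events judged related.

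If the true rate *p* is the same in both arms, and the shares are *a* (plasma) and *b* (placebo):

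reported risk ratio = (*p* × *a*) / (*p* × *b*) = *a* / *b*.

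The true rate cancels, so the ratio depends only on the shares.

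**Step 4: no true difference, assumed true rate 10% in both arms.** Expected events are 30 × reported rate.

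| Share judged related, plasma v placebo | Reported rate | Expected events per 30 | Risk ratio |
|---|---|---|---|
| 50% v 50% | 5% v 5% | 1.5 v 1.5 | 1.0 |
| 60% v 40% | 6% v 4% | 1.8 v 1.2 | 1.5 |
| 80% v 50% | 8% v 5% | 2.4 v 1.5 | 1.6 |
| 80% v 20% | 8% v 2% | 2.4 v 0.6 | 4.0 |
| 20% v 10% | 2% v 1% | 0.6 v 0.3 | 2.0 |

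In the last row 80% of plasma events and 90% of placebo events drop out of the count. At an assumed true rate of 20%, shares of 80% v 20% give 16% v 4% (4.8 v 1.2 events), and the risk ratio is again 4.0.

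**Step 5: a true excess that disappears.** Suppose true rates of 20% on plasma and 10% on placebo, and shares of 10% and 20%. The reported rates are 0.20 × 0.10 = 2% and 0.10 × 0.20 = 2%. A real two-fold excess then reads as a risk ratio of 1.0.

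**Step 6: counting regardless of relation.** Both shares become 100%. Equal true rates give an expected ratio of 1.0, and the two-fold excess in Step 5 reads as 20% v 10%.

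A probability of a significant result would add little here. Section 2.2 names no test for this outcome, and counts this small are poorly served by the usual approximations. With about 3 true events per arm (30 × 10%), reclassifying one or two changes the picture.

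**The case against.** The strongest reply is that no relatedness judgement is described at all. The protocol names no assessor, no causality step and no criteria, and under reading B nothing is filtered. This stands as far as it goes. A reader might infer that the outcome, followed as written, is certain to be filtered differently by arm. The text does not support that. It supports only that the wording permits such filtering.

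A reader might also infer that the comparison would show attribution by site staff instead of event rates. That goes too far on two counts. The formula above shows a mixture of the two, not a replacement. That staff would judge is itself an inference: the protocol says that trained personnel apply the plasma, but not who assesses side effects.

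Third, treatment need not mean plasma. The synopsis calls plasma and placebo the two treatment groups, so a reaction after a placebo application could properly be called related to treatment. This weakens the argument that placebo events would rarely be attributed, and makes extreme shares such as 80% v 20% less plausible. It does not make the shares equal.

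Fourth, section 7 is a qualified risk statement and not an instruction to assessors. It also allows that therapy-associated risks may occur, though at low frequency. It may colour judgement, but no more than that can be said.

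Finally, the visit schedule documents side effects without the qualifier, so an unfiltered count may be recoverable, and tabulation is commonly left to a statistical analysis plan. The first half is why the fix is cheap. The second half does not dispose of the point, because the protocol itself fixes the qualifier in the outcome definition and a later plan would inherit it.

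**Conclusion.** The point holds as a defect of wording that leaves a route to bias open. It depends on two conditions that the protocol neither states nor rules out: that events are screened for relation to treatment before they are counted, and that whoever screens them knows the arm. If both hold, the reported risk ratio is the true ratio multiplied by the ratio of attribution shares. The documents give no shares, so direction and size are unknown. The ratios of 1.5 to 4.0 in the table are illustrations under assumed shares, and the bias is zero if the shares are equal.

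The matter concerns a secondary outcome. No primary outcome, sample size or other stated figure changes. The change is still worth making, because it removes the ambiguity and the possible bias at little cost.

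**What to change.** Reword the item in section 2.2 along these lines: local side effects (keloid formation, skin irritation, local bleeding, proliferative skin reaction, other), counted and compared between arms regardless of judged relation to treatment. Take the counts from the side effects already documented at every visit, and state there that events are recorded without regard to presumed cause. Report judged relatedness only as an added description.

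The cost is one line of text and one extra table, with no new visits or data. More events will be reported in both arms, including background events of wound care, and the report should explain that.

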## **3 Study-design**

### **3.1 General design**

This study is a prospective, randomized, patient-blinded, placebo controlled bi-center study. The study will evaluate whether application of cold atmospheric plasma will accelerate wound healing in diabetic foot patients presenting with wound Wagner-Armstrong 1B or 2B.

